### Data collection

All participants will be assessed at baseline and at four and six months after randomization. The instruments that will be used are all self-report questionnaires, which will be completed on paper by the participants. Trained psychologists who are blind to the group assignments will be present to assist the adolescents if necessary.

### Data management

After the participants have completed the questionnaires, the data will entered into a secure platform, without identifying information (each participant will be assigned an ID number). The original copies of the instruments will be filed and stored, under lock and key, in the principal investigator’s office, along with the list linking the participants’ names and ID numbers. Only two research assistants, in charge of data entry, and the statistician will have access to the database.

### Data analysis

Data and presentation of the results will be in accordance with CONSORT guidelines for randomized clinical trials, with the primary comparative analysis being conducted on an intention-to-treat basis. Initially, we will conduct descriptive analysis to assess the balance between the two groups. The primary analysis will employ multivariable linear regression to investigate differences in mean symptom scores (primary outcome measure) between groups at four months after randomization, adjusting for baseline outcome variable if imbalances are identified. Sensitivity analysis making different assumptions will be conducted to investigate the potential effects of missing data. Similar analyses will be conducted for the secondary outcome measures.

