**Methods and design:**

This is a two-arm, single-blind, randomized controlled trial with a target enrollment of 216 depressed adolescents between 15 and 19 years of age, attending four primary care clinics in Santiago, Chile. In the active arm, depressed adolescents will receive eight sessions of computer-assisted CBT, led by trained psychologists on a weekly basis. In the control arm, depressed adolescents will receive treatment as usual from the primary care centers. Mean depression scores and indicators of dysfunctional thoughts, problem-solving strategies, and health-related quality of life will be measured at baseline and four and six months after randomization.

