### Sample size

We anticipate that the intervention, will produce a clinically meaningful improvement (remission) in 60% of adolescents and only 40% of those in usual care will reach this level of improvement in four months. A difference of 20% will be regarded as worth detecting and clinically meaningful. For a two-sided alpha coefficient of 5% and a statistical power of 80%, 97 adolescents will be needed in each group to detect this difference, or 108 subjects per group, allowing for 10% attrition. This total also yields an 80% power to detect a difference in mean of at least 0.4 standard deviations in the primary outcome measure.

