### Group assignment

Those adolescents who at baseline assessment meet the inclusion criteria and do not meet the exclusion criteria will be randomly assigned to the intervention arm or to the control arm. Blocked (size of four), stratified randomization will be used. Stratification will be implemented regarding sex and severity of depression (mild, moderate, and severe) according to BDI score. Randomization will be generated using web-based random allocation algorithms. Allocation concealment will be carried out by keeping treatment assignment in numbered sealed envelopes in a central place; the envelopes will be opened by individuals who do not participate in the recruitment process.

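### Baseline BDI should always be in the primary regression; adjusting only when an imbalance is seen leaves the model open and gives up precision at no saving

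*Protocol article*

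**What the plan says.** The Data analysis section sets an order. The two groups are first described to assess balance. A multivariable linear regression then compares mean BDI between arms at four months, "adjusting for baseline outcome variable if imbalances are identified". That baseline value is the only covariate named. The section adds: "Similar analyses will be conducted for the secondary outcome measures".

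Two other parts of the article bear on this. Under Group assignment: "Stratification will be implemented regarding sex and severity of depression (mild, moderate, and severe) according to BDI score". Under Data collection, every participant is assessed at baseline, so baseline BDI will be available for everyone.

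The Sample size section asks for "97 adolescents will be needed in each group to detect this difference, or 108 subjects per group, allowing for 10% attrition", and adds: "This total also yields an 80% power to detect a difference in mean of at least 0.4 standard deviations in the primary outcome measure".

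**The concern.** The rule ties adjustment to the wrong thing. Baseline BDI belongs in the model because it explains part of the variation in four-month BDI. That holds in every randomised sample, balanced or not. Waiting for an observed imbalance has three consequences.

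- **The primary model is not fixed.** There are two candidate models and two candidate results, and which one counts is settled after baseline data by arm have been inspected.
- **Precision is lost** whenever the rule selects the unadjusted model.
- **Analysis and design do not match.** Stratifying on BDI severity makes the arms more alike on a prognostic score, so the treatment estimate varies less from trial to trial. An unadjusted regression does not see this. It reports too large a standard error, and its test is conservative.

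At stake are the width of the confidence interval for the main result, and the ability to show that the choice of model owed nothing to the data.

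**Working it through.** **1. The plan's own figures.** Inputs from Sample size: 60% against 40%, two-sided 5%, 80% power, 10% attrition, 0.4 SD.

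- Per group for proportions: [1.96·√(2·0.5·0.5) + 0.8416·√(0.6·0.4 + 0.4·0.6)]² / 0.2² = 96.9, so 97.
- With attrition: 97/0.9 = 107.8, so 108 per group and 216 in total.
- Power for 0.4 SD, unadjusted, 97 per group: 0.4/√(2/97) = 2.786, and Φ(2.786 − 1.96) = 79.6% (79.2% with the exact t distribution).

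The stated 97, 108 and 80% all reproduce. The 80% is the power of an unadjusted comparison.

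**2. What adjustment offers by formula.** Let r be the correlation between baseline and four-month BDI. The article does not give r, so 0.2 to 0.6 is an assumed range. Adjusting multiplies the residual SD by √(1 − r²), so power is Φ(0.4/[√(1 − r²)·√(2/97)] − 1.96):

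- r = 0.2: Φ(2.843 − 1.96) = 81.1%
- r = 0.3: Φ(2.920 − 1.96) = 83.2%
- r = 0.5: Φ(3.217 − 1.96) = 89.6%
- r = 0.6: Φ(3.482 − 1.96) = 93.6%

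Setting these against 79.6% would overstate the gain, because 79.6% ignores the stratified allocation.

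**3. The comparison under the planned design.** Simulation: 216 randomised in six strata (sex by three severity levels) with blocks of four, 194 analysed after random loss, normally distributed scores. The severity mix and sex ratio are assumptions.

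| Assumed r | Power at 0.4 SD, unadjusted | Power at 0.4 SD, baseline BDI always in | Type I error, unadjusted |
|---|---|---|---|
| 0.2 | 79.3% | 80.7% | – |
| 0.3 | 79.7% | 82.8% | 4.2% |
| 0.5 | 82.1% | 89.2% | 3.6% |
| 0.6 | 83.1% | 92.9% | 2.5% |

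The differences in power are 1.4, 3.1, 7.1 and 9.8 points. A repeat with equal severity thirds, 75% in one sex and 10,000 runs per scenario gave powers within one point of these. It gave unadjusted type I errors of 4.2%, 2.8% and 2.3% at r = 0.3, 0.5 and 0.6. With adjustment, type I error stayed close to 5%.

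**4. Why the unadjusted test is conservative.** In the repeat run at r = 0.5 with no treatment effect, the unadjusted regression reported an average standard error of 0.144, while the estimate actually varied with SD 0.130. The ratio is 0.144/0.130 = 1.11. The effective critical value is thus about 1.96 × 1.11 = 2.17, a two-sided error of about 3%, in line with the simulated rate. Always adjusting brought the actual SD to about 0.124.

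**5. If the stratification factors are already in the model.** With sex and severity category as covariates, the repeat run gave 80.2%, 82.5%, 87.0% and 89.9% at r = 0.2, 0.3, 0.5 and 0.6. With continuous baseline BDI it gave 80.8%, 83.3%, 89.3% and 93.0%. The remaining gap is about 1 to 2 points up to r = 0.5 and about 3 at r = 0.6.

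**6. How much turns on the choice of model.** At a true 0.4 SD, the unadjusted and adjusted models fell on different sides of p = 0.05 in about 4%, 9% and 12% of simulated trials at r = 0.3, 0.5 and 0.6.

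**The case against.** The strongest reply has four parts.

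- **The trial keeps its planned power.** This stands. The stated 80% reproduces without adjustment, and nothing here makes the trial underpowered.
- **The data inspected are baseline data, and false positives do not increase.** This stands for a rule applied mechanically to baseline data alone: simulated type I error was below 5%. A reader might infer inflated error from a model chosen after looking at data; the check does not support that.
- **The word multivariable may mean that the stratification factors are included.** This is possible. The article names none, but if they are in, most of the loss disappears (step 5).
- **A condensed article need not define imbalance.** Agreed. A missing threshold is not the point. The rule itself is stated, and a fuller plan that followed it would still make adjustment conditional.

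Three stronger readings are tempting and should not be drawn.

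- **That adjusting at r = 0.5 is worth 129 rather than 97 patients per arm**, from 97/(1 − 0.25). That compares with a t-test under simple randomisation. Stratification already gives the estimate much of that precision, and a good part of the remaining loss comes from the overstated standard error.
- **That the rule would virtually never adjust.** This depends on a cut-off the article does not give. Baseline BDI differed by more than 0.2 SD in about 1% of simulated trials, but by more than 0.1 SD in about 21%. Nor does it carry over to the secondary outcomes, whose baselines are not stratified on.
- **That dropout related to severity would bias the unadjusted result.** This is conditional on a pattern for which the article gives no figures, and sensitivity analyses for missing data are already planned.

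**Conclusion.** The point holds as one of forgone precision and an open primary model. Under the planned stratified blocks with 194 analysed, making baseline BDI unconditional raises power at 0.4 SD by about 1 point at r = 0.2, 3 at 0.3, 7 at 0.5 and 10 at 0.6. If the stratification factors are already covariates, the gain is about 1 to 3 points. The unadjusted test is conservative under this design, with type I error of roughly 4% falling to 2.5% as r rises from 0.3 to 0.6.

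These sizes rest on assumed correlations, an assumed severity mix and sex ratio, normally distributed scores and random loss. The direction does not depend on the particular value of r, provided baseline BDI predicts four-month BDI. Because the design still meets its stated power, this is a free improvement and does not call the trial's validity into question.

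**What to change.** Replace the conditional clause in the Data analysis section with:

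> *The primary analysis is a linear regression of four-month BDI on arm, always including baseline BDI as a continuous covariate and sex (the other stratification factor), whatever the observed balance.*

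State the same for each secondary outcome, using its own baseline value in place of BDI. Report the unadjusted comparison as supportive only. The descriptive table of baseline characteristics can stay, but should not decide the model.

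The cost is one or two sentences. Baseline values are already collected on everyone, so no patients, visits or questionnaires are added. The change should be recorded before anyone sees outcomes by arm, so that the choice of model can be shown to be independent of the result.

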### Monitoring

The primary care center staff will be told to report any type of adverse event (for example, hospitalization, pregnancy, suicide attempt) affecting the participants to the principal investigator, who will then take appropriate measures to ensure the safety and wellbeing of the participants.

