### Inclusion and exclusion criteria

Depressed adolescents aged between 15 and 19 years of age will be invited to participate. Informed consent will be obtained from each participant over 18 years of age, and from the parent or guardian of under-age participants. In the case of the latter, informed assent from the participants will also be required to continue with the study. Depression will be assessed with the Beck Depression Inventory (BDI)
[22]. Adolescents scoring ten or more points on the BDI will be invited to a semi-structured diagnostic interview that includes the Kiddie-SADS-Present and Lifetime Version interview (K-SADS-PL)
[23] to assess other inclusion criteria (diagnostic criteria for depressive disorders) and to ensure that they do not meet the exclusion criteria (current suicidal risk requiring in-patient care, current psychosis, alcohol or substance dependence, or low intellectual ability). Those taking antidepressants or receiving psychotherapy, and those with a history of bipolar illness, will also be excluded. The K-SADS-PL interview will be conducted with all potential participants by the principal investigator (VM), who is a child and adolescent psychiatrist, or a clinical psychologist, who have both been certified in conducting the interview.

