### Intervention arm

The intervention arm will receive eight sessions of computer-assisted CBT plus usual medical treatment, as described in the AUGE Clinical Guidelines for Depression. Computer-assisted CBT sessions will be delivered on a weekly basis and assisted by trained psychologists in face-to-face meetings. The program is called ‘Yo pienso, siento y actúo mejor’ (YPSA-M); in English, ‘*I think, feel, and behave better*’. Topics covered in the program will include information on symptoms and causes of depression, treatment options, problem-solving techniques and other cognitive-orientated strategies to challenge negative thoughts. Copies of the computerized program are available upon written request to the principal investigator (VM).

Psychologists delivering the intervention will receive 12 hours of training and will be supervised by the study principal investigator (VM) once a month, and upon request.

Between sessions, members of the study team will contact the participants to remind them of upcoming appointments in the intervention arm.

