### Control arm

The control arm will receive treatment as usual from the primary care clinics. The professionals in the primary care centers will be instructed to follow the AUGE Clinical Guidelines for Depression.

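### The one stated adverse-event route is unsolicited reporting by clinic staff, with unequal scheduled contact by arm, so harms may be ascertained unequally and serious events missed

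*Protocol article*

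**What the plan says.** All references are to the protocol article.

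- **Reporting route (Monitoring).** "The primary care center staff will be told to report any type of adverse event" affecting participants, and the report goes to the principal investigator. The examples given include hospital admission and suicide attempt. The instruction does not distinguish the arms.
- **Intervention arm.** "The intervention arm will receive eight sessions of computer-assisted CBT plus usual medical treatment". On their delivery: "Computer-assisted CBT sessions will be delivered on a weekly basis and assisted by trained psychologists in face-to-face meetings". Between sessions, "members of the study team will contact the participants to remind them of upcoming appointments in the intervention arm". The psychologists are supervised monthly, and on request, by the principal investigator, who also receives the event reports.
- **Control arm.** "The control arm will receive treatment as usual from the primary care clinics". No number of contacts is given.
- **Common assessments (Data collection).** "All participants will be assessed at baseline and at four and six months after randomization". These consist of paper self-report questionnaires. Blinded psychologists are there to help if needed; no enquiry about events is described.
- **Population (Inclusion and exclusion criteria).** The exclusion for suicidality is limited to "current suicidal risk requiring in-patient care", so adolescents at lesser risk can be enrolled.
- **Blinding (Methods and design).** Only the outcome assessor is blinded.

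**The concern.** Under the stated rule, an event enters the trial record if clinic staff come to know of it and pass it on. That depends on the participant's contact with the clinic, and the contact the article describes is not the same in the two arms. The reporters are also not described as blinded.

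Two things are at stake. First, a participant who stops attending may be admitted to hospital or attempt suicide without the trial learning of it, although two follow-up assessments are planned for that person. Second, if harms are later tabulated by arm, a difference could reflect who was seen more often rather than who had more events, and a reader could not tell which.

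**Working it through.** **1. The plan's own figures.** The article states no adverse-event rate and no detection rate. The only figure used below is the 108 per arm in Sample size, which reproduces:

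- Inputs: remission 60% versus 40%, two-sided alpha 5%, power 80%, pooled variance under the null.
- n = [1.96 × √(2 × 0.5 × 0.5) + 0.8416 × √(0.6 × 0.4 + 0.4 × 0.6)]² / 0.2² = [1.386 + 0.583]² / 0.04 = 96.9, so 97 per arm.
- With 10% attrition: 97 / 0.90 = 107.8, so 108 per arm.

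**2. Opportunities for an event to become known, side by side.**

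| | Intervention | Control |
|---|---|---|
| Instruction to clinic staff | yes | yes, the same |
| Usual care | yes | yes; contact count not stated |
| Weekly face-to-face sessions | eight | none stated |
| Study-team reminder contacts | yes | none stated |
| Therapists supervised by the recipient of reports | monthly and on request | none stated |
| Four- and six-month assessments | questionnaires; no event items stated | the same |

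The only contacts that are equal by design are the assessments in the last row, and the article gives them no part in capturing events.

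**3. How large could the distortion be?** Let p be the true risk, equal in both arms, and let d_I and d_C be the probabilities that an event is recorded in the intervention and control arms. Expected recorded events are 108 × p × d in each arm. The ratio is (p × d_I) / (p × d_C) = d_I / d_C, so it does not depend on p. All values of p and d below are assumptions. With p = 10%, 108 × 0.10 = 10.8 true events per arm:

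| d_I | d_C | Recorded, intervention | Recorded, control | Ratio |
|---|---|---|---|---|
| 80% | 80% | 8.6 | 8.6 | 1.00 |
| 90% | 80% | 9.7 | 8.6 | 1.125 |
| 90% | 60% | 9.7 | 6.5 | 1.50 |
| 90% | 50% | 9.7 | 5.4 | 1.80 |

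**4. Allowing for the length of the sessions.** The rows with 90% in the intervention arm hold that rate for the whole follow-up. Eight weekly sessions cover about 8 of roughly 26 weeks, a share of 8/26 = 0.31. Assume constant risk over time, and equal detection in both arms once sessions end:

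- d_C = 50%: d_I = 0.31 × 0.90 + 0.69 × 0.50 = 0.62; ratio 0.62 / 0.50 = about 1.25.
- d_C = 60%: d_I = 0.31 × 0.90 + 0.69 × 0.60 = 0.69; ratio 0.69 / 0.60 = about 1.15.

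The assumed range is therefore 1.0 to 1.8. The values at the upper end need the session effect on detection to persist long after the sessions have finished.

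**The case against.** The strongest reply is that this is a condensed article. Monitoring does not say that clinic staff are the sole source, nothing bars therapists or assessors from reporting, and event forms usually sit in the full protocol, which is not shown. That limits the claim to the route the article states. It does not remove the point, because the article sets out a definite rule and a better one is available at visits already planned.

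Other objections stand as limits:

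- A reader might infer that harms **are** detected unequally. The documents do not show this; it is a risk inferred from the design.
- A reader might count **eight extra contacts** as the net difference. Control clinics are told to follow the national guideline, which, according to Background, includes medical controls and psychosocial interventions. Other outcomes says attendance is monitored in both arms. The net difference is unknown.
- It is not stated whether the psychologists giving the sessions, or those making reminder contacts, count as clinic staff. If they do, the intervention arm offers more occasions to report. If they do not, the sessions feed the stated route only indirectly, for example through supervision, and a therapist who hears of an event has no stated duty to report it. Both readings call for clarification.
- A reader might conclude that **the trial's safety comparison is biased**. The aims, hypotheses, outcomes and analysis name no safety endpoint or between-arm test, and Monitoring is directed at participant welfare. Bias can concern only harms that are reported by arm.
- Asking about events in person could unblind the assessor, the only blinded party. The fix has to respect that.

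**Conclusion.** The point holds as a cheap improvement, not as an error in the efficacy design. As described, capture of adverse events rests on unsolicited reports from staff not described as blinded, with more scheduled contact stated for one arm. Ascertainment may differ by arm, and serious events may be missed in participants who disengage from the clinic.

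The size cannot be derived from the document. On assumed rates the spurious ratio lies between 1.0 and 1.8, with about 1.1 to 1.25 under the milder assumptions. Quoting only 1.5 to 1.8 would overstate what is known. Every illustration supposes that any difference favors detection in the intervention arm, which the article does not establish. The concern about missed events does not need that assumption, nor a planned comparison. Confidence is moderate because the full protocol may name further routes. The sample size and the primary and secondary analyses are unaffected.

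**What to change.** Make three changes in Monitoring and Data collection:

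1. Add to the paper self-report questionnaires at four and six months, in both arms, the same few fixed items on hospital admission, pregnancy and suicide attempt since the last assessment. Word them so that they do not reveal the treatment received, and where possible have the answers checked by someone other than the blinded assessor.
2. State that study therapists and assessors, as well as clinic staff, report any event they learn of to the principal investigator.
3. Base any by-arm table of harms on the fixed items, and list spontaneous reports separately.

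The cost is a few minutes per assessment and a short ethics amendment, with no new visit or staff. More events will probably be recorded. A small unblinding risk remains. The items will not capture events in participants who miss the assessments; the planned attrition allowance is 108 − 97 = 11 per arm, and those who leave care may be among them. Reports from clinic staff and therapists remain necessary for that group.

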### Research governance and ethics

#### Trial management

The study will comply with local Research Governance requirements.

